### Statistical analysis

Statistical analyses will be performed by an independent statistician using the statistical software IBM SPSS Version 25.0 (IBM Corp.). The study will use per-protocol set (PPS) as the primary method of analysis, with full analysis set (FAS) analysis as secondary confirmation, if necessary. The PPS analysis will be applied to patients who are fully compliant with the protocol. In this study, data from patients who comply with IP (≥ 80%), assess the primary efficacy endpoint, and complete the study without major protocol violations will be included in the analysis. The FAS population will consist of data from patients who meet the inclusion criteria, have taken the IP at least once, and have at least one endpoint measurement. The safety analyses set will include all data from patients who received at least one dose of IP after randomization.

For the comparative evaluation of demographic or clinical characteristics between groups, two-sample t-tests will be performed for continuous data, and the chi-squared test or Fisher's exact test will be used for dichotomous data. If significant differences are found between the groups, one-way analysis of covariance will be conducted for continuous data, and logistic regression will be performed for dichotomous data to correct the imbalance.

The basic principle of statistical analysis for the efficacy endpoints is the comparison of data between the two groups after the 4-week treatment intervention. For the efficacy endpoint at week 4, a one-sided 97.5% confidence interval will be calculated to confirm non-inferiority (*p* < 0.025) by determining the difference in mean changes of the questionnaire score between the treatment and control groups. All measurements will be presented as mean ± standard deviation or as percentages (n %). Mean comparisons between groups will be conducted using a two-sample t-test as a parametric method or a Mann–Whitney test as a non-parametric method. Differences within each group between baseline and measurements after a specific period will be analyzed using either the paired t-test or the Wilcoxon signed-rank test. Repeated measures will be analyzed to compare the changes in the mean value of the same variable measured over time between the two groups. For safety assessments, the incidence of adverse and serious adverse events will be calculated and tested by group using the chi-square test or Fisher's exact test. Differences in effectiveness between subtypes, where applicable, will be determined by analysis of variance, considering participant characteristics (such as sex and age), GERD classification (including EE and NERD), previous PPI therapeutic dosage, GERD pattern identification, and other clinical characteristics.

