#### Medication compliance assessment

Participants in each group will receive IP at visits 1 (week 0) and 2 (week 2). The investigator will check the number of remaining medications to ensure that the participant had taken the medication as directed (visits 2 and 3). The medication compliance rate (%) will be calculated every 2 weeks by dividing the number of medications actually taken by those that should have been taken, with a threshold of 80% for efficacy analysis.

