### Sample size calculation

The results of previous study were used to determine the non-inferiority margin required to calculate the sample size [42]. The upper limit of the 95% confidence interval for the mean difference in the degree of improvement of FSSG between the test and control groups after 4-week treatment was estimated to be -8.29. Assuming a significance level of 2.5%, a statistical power of 90%, and a 1:1 allocation ratio, 86 participants (43 per group) would be required to account for a dropout rate of 30%, considering the larger standard deviation of 9.8.

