## Discussion

To our knowledge, many clinical studies have shown the substantial efficacy of YGJ and PPIs in relieving GERD symptoms safely. However, no double-blind studies have been conducted on combination therapy with YGJ and PPI using each placebo in patients with rGERD. Therefore, this study aims to verify the non-inferiority of combination treatment compared to conventional rGERD treatment using a double-dummy design.

Sample data from the Health Insurance Review and Assessment Service on patients with GERD in South Korea showed that a substantial proportion of patients with GERD were taking PPIs for at least 12 weeks, with the prevalence and prescribed daily dose of PPIs gradually increasing, combined with high medical costs [43].

Nowadays, there is no consensus regarding the diagnostic criteria for rGERD [44]. Although there may be differences in the definitions regarding the dosage and duration of antacids and how to assess symptomatic improvement, approximately 45% of patients with GERD are partially or completely unresponsive to PPIs, and there is a need to develop more effective treatments [45]. Therefore, the definition of "refractory" in this study includes patients who have been treated with PPIs in the past but have not responded adequately to standard short-term PPI therapy, including those who 1) have recurrent symptoms, 2) have been on maintenance therapy for a period of time, and 3) are taking medication as needed for recurrent symptoms.

Based on the opinions of gastroenterologists, safety reports in previous studies, and clinical utility, RPZ was selected as the PPI for use in this trial. Based on previous research articles published in Japan and drug information registered with the Ministry of Food and Drug Safety, the initial dose for symptomatic relief of GERD (including both EE and NERD) in this study was set at 10 mg/day of RPZ [24, 32]. In addition, we confirmed the clinical utilization of the PPI twice daily oral dosing strategy according to the guidelines for patients with poorly controlled GERD and set it as a control group for the combination of botanical drugs [5].

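### Non-inferiority can be declared from a per-protocol set selected after randomisation, because the full-set analysis is optional and need not agree

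*Protocol article*

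**What the plan says.** The Discussion gives the aim: "this study aims to verify the non-inferiority of combination treatment compared to conventional rGERD treatment using a double-dummy design". Under Statistical analysis the hierarchy of sets is: "The study will use per-protocol set (PPS) as the primary method of analysis, with full analysis set (FAS) analysis as secondary confirmation, if necessary". Nothing in the article says when the second analysis becomes necessary.

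Membership of the PPS requires compliance of at least 80%, an assessed primary endpoint and a clean completion; only patients who "complete the study without major protocol violations will be included in the analysis". The compliance limit also appears under Medication compliance assessment, where compliance is computed every two weeks, "with a threshold of 80% for efficacy analysis". The FAS is wider. Its members must meet the inclusion criteria, "have taken the IP at least once, and have at least one endpoint measurement".

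The decision rule is that "a one-sided 97.5% confidence interval will be calculated to confirm non-inferiority" at week 4, with p < 0.025. It does not say in which set. The Sample size calculation section arrives at 43 per group, a number that "would be required to account for a dropout rate of 30" per cent.

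**The concern.** Every condition for the PPS other than eligibility is settled after randomisation and can depend on how the patient is doing. A patient who stops because the assigned treatment is not working leaves the primary analysis. If this happens more in the test arm, the remaining test patients look better than the arm as a whole, and the comparison shifts towards non-inferiority.

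A full-set analysis has its own weakness in a non-inferiority trial, since including patients who did not take the treatment can dilute a real difference. Neither set is reliably conservative, so the usual protection is to run both and require them to agree. Here the second analysis is discretionary and has no part in the decision rule. The conclusion could be drawn without it, or kept in spite of it.

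**Working it through.** **Inputs from the Sample size calculation section:** margin magnitude 8.29 FSSG points (the text has the limit "between the test and control groups after 4-week treatment was estimated to be -8.29"; its use as the margin is inferred, because it reproduces the sample size), SD 9.8, significance level 2.5% (taken as one-sided), power 90%, 1:1 allocation, dropout 30%.

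**1. The plan's own figure.** n per arm = 2 × 9.8² × (1.960 + 1.282)² / 8.29² = 29.37, so 30. Allowing for dropout, 30 / 0.70 = 42.9, so 43 per arm and 86 in total. This matches. The plan therefore sizes its verdict on 30 of 43 per arm, or 60 of 86 = 69.8%.

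**2. A check by hand.** Suppose 13 of 43 are excluded per arm, control exclusions are unrelated to response, and the true difference among all randomised patients is exactly 8.29. If the excluded test patients do worse than the retained ones by D points, the PPS difference is too favourable by (13/43) × D. The standard error with 30 per arm is 9.8 × √(2/30) = 2.53. The false-claim rate is about Φ(−1.96 + shift/2.53).
- D = 4: shift 1.21, Φ(−1.48) = about 7%.
- D = 8: shift 2.42, Φ(−1.00) = about 16%.

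The values of D are assumptions.

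**3. Simulation under three patterns of loss.** 43 per arm, SD 9.8, true difference 8.29, about 30% loss overall, pooled t-interval. The log-odds of leaving rise by 0.5 or 1.0 per SD of poorer response (assumed). False non-inferiority in the PPS:

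| Pattern of loss | 0.5 per SD | 1.0 per SD |
|---|---|---|
| Both arms select equally around their own mean | about 2.5% | about 2.5% |
| One common rule on absolute response | about 3.5% | about 7% |
| Informative in test arm, random in control | about 8% | about 16% |

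**4. What the second set adds.** This depends on whether leavers have a week-4 value. In the least favourable pattern (bottom row):
- all leavers have a week-4 value: requiring both sets holds the error at about 2%;
- half of them lack it: about 4% and 6%;
- all of them lack it and observed cases are analysed: the two sets coincide, the error stays at about 8% and 16%, and requiring both gains nothing.

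**5. Cost in power.** At a true difference of 0 with non-informative exclusions:
- PPS alone, 30 per arm: Φ(8.29/2.53 − 1.96) = Φ(1.32) = 0.906 (0.896 with the t distribution);
- FAS, 43 per arm with a week-4 value for all: standard error 9.8 × √(2/43) = 2.11, power about 0.97;
- both together, simulated with the PPS nested in the FAS: about 0.89.

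The loss against the PPS alone is under one point, with no change in N.

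**The case against.** A per-protocol primary analysis is a recognised convention for non-inferiority, and the article does name the FAS as confirmation. Both points stand. The PPS is not an error in itself, and it would be too strong to say that the plan rests on the PPS alone. What remains is that the confirmation is conditional on an undefined trigger and plays no part in the rule. An SAP that is not shown may define the trigger, but the article itself states the hierarchy, so this is not merely a missing detail.

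The trial is double-blind and double-dummy, so patients do not know their arm, and nothing in the documents shows that loss will be informative in one arm only. This also stands. A reader might take 8% to 16% as the expected error, but those figures belong to the least favourable pattern; with equal selection in the two arms there is no inflation.

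A reader might also infer that test-arm failures must leave more often because that arm has half the acid suppression. The documents do not support this. They give half the rabeprazole dose (10 against 20 mg/d) plus YGJ, which they describe as prokinetic; dose is not a measure of acid suppression. Nor is 70% a forecast of the PPS. It is the planning allowance for dropout. The actual share could be higher if fewer drop out, or lower because non-compliance and major violations also exclude patients.

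Finally, the planned FAS does not require a week-4 value, and true dropouts may have none. This objection is correct and shapes the remedy: making the FAS mandatory protects little unless those values are collected.

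**Conclusion.** The point holds in a limited form. As written, the non-inferiority verdict can come from a subset selected after randomisation, with no obligation to run the wider analysis or to have it agree. That follows from the text and needs no assumption.

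The size of the risk does rest on assumptions. With selection of 0.5 or 1.0 log-odds per SD, the false-claim rate at the margin ranges from no inflation (about 2.5%) to about 8% or 16%, depending on whether poor responders leave the two arms alike. The documents do not show which pattern will apply. The sample size arithmetic is correct and is not in dispute here. This is a cheap and worthwhile improvement; it does not show that the trial's conclusion will be wrong.

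**What to change.** In the Statistical analysis section, delete the condition on the FAS and make that analysis mandatory. State that non-inferiority is claimed only if the confidence limit meets the margin in both the PPS and the FAS, with patients analysed as randomised.

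In the same amendment, provide for continued collection of the week-4 FSSG, by phone if needed, from patients who stop the investigational product. The Outcome measures section already has a week-8 phone visit, and the FSSG is scheduled at every visit after screening, so phone collection should be practicable. The two changes belong together, because without the week-4 values the sets nearly coincide.

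The cost is under one point of power when exclusions are non-informative, one further analysis, and some phone questionnaires. Since recruitment has begun, the follow-up change needs a protocol amendment, and both changes should be fixed before unblinding. Week-4 values already missed for early leavers may not be recoverable.

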## Methods

### Study design

This study is a single-center, randomized, double-blind, double-dummy, parallel-design clinical trial to evaluate the safety and efficacy of co-administered YGJ and PPI for rGERD. Patient recruitment has already commenced in August 2023 and will continue until February 2025 at the Kyung Hee University Korean Medicine Hospital (Seoul, Republic of Korea).

A total of 86 participants who fulfill the study criteria and consent to participate will be randomized in a 1:1 ratio for the test (43 participants; YGJ and RPZ 10 mg/d) and control (43 participants; RPZ 20 mg/d) groups. The study will consist of a screening visit and 4 weeks of treatment (weeks 0–4), followed by 4 weeks of follow-up (weeks 4–8).

In this study, the principal investigator (PI) and researchers will follow lawful procedures based on ethical principles, including the principles of the Declaration of Helsinki, to provide participants with detailed study information and obtain informed consent for participation. Participants are free to withdraw from the study at any time for any reason.

This study will be conducted according to an approved protocol by the Institutional Review Board (IRB) of Kyung Hee University Korean Medicine Hospital and will adhere to the Good Clinical Practice standards established by the Korean Food and Drug Administration. The study will also follow the Standard Protocol Items: Recommendations for Interventional Trials (SPIRIT) and the Consolidated Standards of Reporting Trials (CONSORT) statement [33, 34]. The flowchart and outcome evaluation points for this trial are shown in Fig. 1 and Table 1.

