### Concomitant drug investigation

During the study period, the participants are prohibited from taking medications that may affect gastric acid secretion and the digestive system, as determined by the investigator, including those mentioned in point 8 of the exclusion criteria. Patients will be able to participate in this study after discontinuing these treatments prior to study entry, following a 2-week washout period. Additionally, patients are prohibited from receiving other treatments stated in point 16 of the exclusion criteria to relieve the symptoms of GERD during the study. At each visit during the observation period, participants will be instructed to report concomitant medications and contraindications. All concomitant medications and treatments will be recorded in the Case Report Form (CRF).

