#### Primary outcome

##### Frequency Scale for the Symptoms of GERD (FSSG)

In addition to the typical symptoms of GERD, the FSSG includes an assessment of dyspeptic symptoms, such as bloating and postprandial fullness. Participants will be required to rate how often they experience each of the 12 symptoms on a scale of 0 (never) to 4 (always), with a total of 48 points, which will be summed by dividing the symptoms into two categories: acid reflux and dysmotility [36]. The FSSG will be measured at all visits except the screening visit, and the change in the FSSG score from baseline to 4 weeks will be calculated. The improvement between the baseline and follow-up period will be compared between the groups to determine the persistence of the treatment effect. In addition, the proportion of participants with no GERD symptoms at one-week recall, referred to as a treatment responder, will be compared between the groups.

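### Read literally, the per-protocol set lets events in weeks 4–8 remove patients with valid week-4 data from the primary non-inferiority analysis; the intended reading is unclear

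*Protocol article*

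**What the plan says.** All references are to the protocol article.

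- **Analysis set (Statistical analysis).** "The study will use per-protocol set (PPS) as the primary method of analysis, with full analysis set (FAS) analysis as secondary confirmation, if necessary". Eligible for the PPS are patients with IP compliance of at least 80% who "assess the primary efficacy endpoint, and complete the study without major protocol violations will be included in the analysis". Having the endpoint assessed and completing the study are listed as separate conditions.
- **Length of the study (Study design).** "The study will consist of a screening visit and 4 weeks of treatment (weeks 0–4), followed by 4 weeks of follow-up (weeks 4–8"). The section on the Overall Treatment Evaluation describes the week-8 contact as a phone visit.
- **Primary endpoint (FSSG).** "the change in the FSSG score from baseline to 4 weeks will be calculated". The test has the same time point (Statistical analysis): "For the efficacy endpoint at week 4, a one-sided 97.5% confidence interval will be calculated to confirm non-inferiority".
- **Medication ban (Concomitant drug investigation).** "During the study period, the participants are prohibited from taking medications that may affect gastric acid secretion and the digestive system". No end at week 4 is given.
- **Use of the follow-up (FSSG).** "The improvement between the baseline and follow-up period will be compared between the groups to determine the persistence of the treatment effect".

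**The concern.** A per-protocol restriction for a week-4 endpoint should rest on what happened up to week 4. Here the completion condition reaches four weeks beyond the last dose and beyond the primary measurement. The enrolled patients have persistent symptoms despite earlier PPI treatment, and the Background says that GERD symptoms return when treatment stops. A lost week-8 contact, or use of an acid-modifying drug after week 4, is therefore foreseeable and may be related to how well treatment worked.

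The plan itself treats persistence of effect as something to compare between arms. If such events decide whether a patient's week-4 score is used, the primary comparison is conditioned on a later, possibly treatment-related outcome, and valid primary data are discarded. The full analysis set (FAS) would keep these patients, but it is only a conditional, secondary check.

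**Working it through.** **1. The rule against the timeline**

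| Element | Time it refers to | Section |
|---|---|---|
| IP given | weeks 0–4 | Interventions |
| Primary endpoint and non-inferiority test | week 4 | FSSG; Statistical analysis |
| Study as defined | screening to week 8 | Study design |
| Medication ban | whole study period | Concomitant drug investigation |
| PPS completion condition | the study | Statistical analysis |

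Take a patient with at least 80% compliance and a week-4 FSSG who cannot be reached at week 8. The first two PPS conditions are met. The third fails if the study means what Study design says. Because endpoint assessment is already its own condition, completion literally adds something to it. For a patient who takes a prohibited drug after week 4, the outcome depends on whether that is classed as major, which the article does not state.

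**2. The plan's sample size**

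Inputs from Sample size calculation: margin 8.29, SD 9.8, significance level 2.5% (used as one-sided), power 90%, dropout 30%. A true difference of 0 is assumed.

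n = 2 × [9.8 × (1.960 + 1.282) / 8.29]² = 29.37, rounded up to 30 per arm. 30 / 0.70 = 42.9, rounded up to 43 per arm, 86 in total. The stated figure is reproduced.

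**3. Power under two readings of the 30% allowance**

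- *It covers losses to week 8.* The exclusions in question are already counted, 43 × 0.70 = 30 per arm remain, and power is not reduced.
- *It covers losses to week 4 only (assumption).* Further exclusions come off the 30. Power is from the noncentral t distribution with 2n − 2 degrees of freedom and noncentrality 8.29 / [9.8 × √(2/n)]:

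| Further loss per arm (assumed) | n per arm | Power | Total N to restore the target |
|---|---|---|---|
| 0 | 30 | 89.6% | 86 |
| 3 (10%) | 27 | 86.2% | 96 |
| 6 (20%) | 24 | 81.8% | 108 |

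The last column is 2 × 30 / (0.70 × 0.90) and 2 × 30 / (0.70 × 0.80), each arm rounded up. The normal approximation used for planning gives 90.6% at 30 per arm.

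**4. Possible shift in the week-4 difference**

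The document gives no exclusion rates, so every input here is an assumption. If a fraction f of an arm is excluded and had improved d points less at week 4 than those retained, that arm's mean improvement rises by f × d.

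- 30% excluded in test, 10% in control, d = 5 to 8: (0.30 − 0.10) × 5 = 1.0 to (0.30 − 0.10) × 8 = 1.6 points in favour of test, or 12% to 19% of 8.29.
- Rates reversed: the same 1.0 to 1.6 points in favour of control.
- Equal rates and equal d: shift 0.

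A second model excludes the worst fraction f on a normal post-treatment outcome in one arm only, with correlation r to the week-4 change. The shift is r × 9.8 × φ(z_f) / (1 − f), where z_f is the f-quantile of the standard normal distribution and φ its density. For f = 10% it is 0.57 (r = 0.3) to 0.96 (r = 0.5); for f = 20%, 1.03 to 1.71. This is about 7% to 21% of the margin, towards whichever arm loses the patients.

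**The case against.** There are five points on the other side.

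- **The word study is not used consistently.** The Discussion, explaining the choice of treatment length, uses study duration for the four treatment weeks, and Statistical analysis bases efficacy on the comparison after the 4-week treatment. Completion could therefore mean reaching week 4. This stands: a reader might infer that weeks 4–8 definitely decide who enters the primary analysis, and the text does not settle that. It does not remove the point, because Study design gives the longer definition and nothing in the PPS rule chooses between them.
- **Major violations are not listed.** An article may leave the list to the full protocol or analysis plan. This stands for the medication route, which is only a possibility. It does not answer the missed week-8 contact, which bears on the completion condition itself.
- **Deducting patients from 30 per arm may count them twice.** This stands. The 30 is what is left after the 30% allowance, and the article does not limit that allowance to week 4. A fall in power to 81.8% is conditional and not shown.
- **The bias has no known direction.** This stands. A reader might infer a bias towards the combination, but the Background hopes that the combination will reduce recurrence. On that expectation more control patients would be excluded for relapse, which would make non-inferiority harder to show.
- **The FAS keeps these patients.** This is true, but the FAS is secondary and is run only if thought necessary, so it softens the problem without removing it.

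**Conclusion.** The point holds as a defect of wording with a real consequence if the wording is applied literally. The PPS rule, set beside the stated eight-week timeline, allows events after the endpoint to exclude patients whose week-4 data are complete, and those events may depend on treatment response. Whether the sponsor intends this cannot be told from the article.

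The document supports no particular size or direction of bias. The shifts of roughly 0.6 to 1.7 points (7% to 21% of the 8.29 margin) follow from assumed rates and correlations, can favour either arm, and largely vanish if exclusion is equal. Any power loss rests on the further assumption that the 30% allowance stops at week 4. The claims that the trial is underpowered, or tilted towards the test arm, are therefore not supported. The case for a change rests on the selection rule itself.

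**What to change.** In Statistical analysis, replace the completion condition for the primary analysis with one tied to week 4: at least 80% compliance over the treatment period, a week-4 FSSG present, and no major protocol violation before the week-4 visit. Apply week-8 completion, and medication taken in weeks 4–8, only to the follow-up analyses. The medication ban itself need not change for this.

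The cost is one sentence. N stays 86, no visit or measurement is added, and the primary analysis keeps at least as many patients as under the literal rule. Trial status reports that recruitment is under way, so the wording should be settled before unblinding.

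### Run as stated, the week-4 two-sample comparison leaves out full analysis set patients without a week-4 FSSG, so the FAS does not check the per-protocol result for dropout

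*Protocol article*

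**What the plan says.** All references are to the Methods of the protocol article.

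- **Analysis sets (Statistical analysis).** The PPS is primary and requires at least 80% compliance, an assessed primary endpoint and study completion without major violations. The FAS is used "with full analysis set (FAS) analysis as secondary confirmation, if necessary". Its members meet the inclusion criteria and "have taken the IP at least once, and have at least one endpoint measurement".
- **Endpoint (Frequency Scale for the Symptoms of GERD).** "the change in the FSSG score from baseline to 4 weeks will be calculated". On timing, "The FSSG will be measured at all visits except the screening visit", so scores exist at weeks 0 and 2 as well as week 4. In addition, "the proportion of participants with no GERD symptoms at one-week recall, referred to as a treatment responder, will be compared between the groups".
- **Test (Statistical analysis).** A one-sided 97.5% confidence interval at week 4 is obtained "by determining the difference in mean changes of the questionnaire score between the treatment and control groups", with a two-sample t-test or Mann–Whitney test for comparing means. A separate sentence plans a repeated-measures analysis over time. It names no model and is not tied to the non-inferiority limit.
- **Dropout (Sample size calculation).** The 86 participants "would be required to account for a dropout rate of 30" per cent.

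**The concern.** The FAS rule and the week-4 test cover different patients. Someone who stops after week 2 has an endpoint measurement and belongs to the FAS, but has no change to week 4. Read literally, a baseline score and one dose are enough to qualify. A two-sample test on week-4 change has no value for either patient.

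This matters because the PPS is primary and excludes these patients by definition. The FAS is the only stated analysis that could show whether early leavers change the conclusion. If it omits them too, neither non-inferiority comparison counts a patient who left because symptoms were uncontrolled. Such departures are plausible, since other treatments affecting acid secretion or the digestive system are prohibited during the study (Concomitant drug investigation). The article does not show that they will occur or that they will differ between arms.

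**Working it through.** **1. The plan's own figure.** Inputs from Sample size calculation: limit 8.29 FSSG points (the stated figure in absolute value, used as the margin), SD 9.8, one-sided 2.5%, power 90%, 1:1 allocation. Assume a true difference of 0.

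n per arm = 2 × [9.8 × (1.960 + 1.282) / 8.29]² = 29.4, rounded up to 30. Then 30 / 0.70 = 42.9, rounded up to 43 per arm, or 86. The plan's figure is reproduced. It already assumes 30 evaluable patients per arm, at which power is 90.6% (normal) or 89.6% (t). The question is therefore bias, not power.

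**2. Who enters each comparison, as stated.**

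| Patient | PPS | In FAS | Has week-4 change |
|---|---|---|---|
| Complies and completes, no major violation | yes | yes | yes |
| Below 80% compliance or major violation, attends week 4 | no | yes | yes |
| Leaves between weeks 2 and 4 | no | yes | no |
| Leaves before week 2 (baseline score only) | no | yes, on a literal reading | no |

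The FAS restores the second row. It does not restore the third or fourth.

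**3. Size of the bias.** Let leavers improve D points less than completers, with dropout pT (test) and pC (control). A comparison of those with week-4 data understates the test arm's loss by δ = D × (pT − pC). At a true all-randomised loss of exactly 8.29, the chance of declaring non-inferiority is approximately 1 − Φ(1.96 − δ/SE), where SE = 9.8 × √[1/(43(1 − pT)) + 1/(43(1 − pC))]. D, pT and pC are assumptions; the article gives none of them by arm.

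SE is 2.53 for both 30/30 and 35/25 dropout, and 2.55 for 40/20.

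| D | 30% v 30% | 35% v 25% | 40% v 20% |
|---|---|---|---|
| 3 | δ 0: 2.5% | δ 0.3: 3.3% | δ 0.6: 4.2% |
| 5 | δ 0: 2.5% | δ 0.5: 3.9% | δ 1.0: 5.8% |
| 10 | δ 0: 2.5% | δ 1.0: 5.9% | δ 2.0: 12.0% |

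Simulation with t intervals (43 per arm, 40,000 runs per cell) agrees: 3.1% and 4.2% at D = 3, 3.9% and 5.7% at D = 5, and 5.8% and 11.8% at D = 10. If dropout is heavier in the control arm, δ changes sign and the bias runs against non-inferiority.

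**4. Responders.** Suppose 40% respond in each arm among those assessed. With 40% v 20% dropout and leavers counted as non-responders, the rates are 0.40 × 0.60 = 24% and 0.40 × 0.80 = 32%. With 30% dropout in both arms, both are 0.40 × 0.70 = 28%.

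**5. Does a model using week 2 help?** I simulated large samples with 40% v 20% dropout driven by week-2 response. The assumed correlation between week-2 and week-4 change was 0.5, and the resulting gap between leavers and completers was about 5 points. The completer comparison was biased by 0.97 points. A likelihood estimate using week 2 was biased by 0.00 when every leaver had a week-2 score, by 0.29 when half left before week 2, and by 0.98 (no gain) when all did.

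**The case against.** The strongest reply is that this is a condensed article. A rule for missing scores and a responder denominator commonly sit in the full protocol or SAP, neither of which is shown. That stands: their absence here is not an error, and the article nowhere says that leavers are dropped. The point rests on what is stated, namely a two-sample test on week-4 change applied to a set that can include patients without one, where the data already collected allow a better method.

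A reader might infer several stronger things that the article does not support.

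- *The FAS rule and the endpoint contradict each other.* They do not; a missing-data rule would reconcile them. Whether the one measurement must be post-baseline is ambiguous, but patients with week 2 only are admitted on either reading.
- *The FAS becomes a completers' set that cannot check the PPS at all.* It still adds non-compliers, violators and those lost between weeks 4 and 8.
- *About 26 of 86 patients will lack a week-4 score.* The 30% allowance (0.30 × 86 = 25.8) may also cover non-compliance, violations and loss after week 4.
- *The bias favours non-inferiority.* The test arm has the lower RPZ dose but adds YGJ, so the direction is unknown.
- *The FAS is confirmatory.* It is secondary and conditional.

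The planned repeated-measures analysis is a partial answer only. It is not linked to the non-inferiority limit, and a complete-case version would omit the same patients.

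**Conclusion.** The point holds in limited form. As stated, the FAS comparison does not test whether the PPS conclusion survives dropout. There is no sample-size error and no loss of power against the plan. The consequence is a possible bias that appears only if dropout is related to response and unequal between arms. With more dropout in the test arm, the false non-inferiority rate rises from 2.5% to about 3–4%, 4–6% or 6–12% for assumed gaps of 3, 5 or 10 points. The 10-point gap exceeds both the SD and the margin figure, so the top of that range is an extreme case. At equal dropout there is no inflation.

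**What to change.** In Statistical analysis:

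1. For the FAS, replace the two-sample t-test on week-4 change with a likelihood-based repeated-measures model on the week-2 and week-4 FSSG, with baseline FSSG, arm, visit and arm-by-visit. Read the one-sided 97.5% limit from the week-4 contrast.
2. Report this result always beside the PPS, instead of only when thought necessary.
3. In the responder proportion, count FAS patients without a week-4 assessment as non-responders.

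Optional additions are collecting the week-4 FSSG by phone from patients who stop early (a phone visit already exists at week 8), and a sensitivity analysis that penalises missing test-arm changes by amounts up to the margin.

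The cost is a change of wording; the week-2 score is already collected. Responder rates may be lower. Patients with only a baseline score still add little information, and the model relies on dropout being explained by the scores observed before it.
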